### Design and setting

Retrospective, observational, population-level cohort study of patients with atrial fibrillation and matched controls using administrative claims data among a 5% sample of fee-for-service Medicare beneficiaries in the United States from 2000–2020. This data source allows us to follow unique patients longitudinally for the duration of their fee-for-service enrollment, regardless of state of residence.

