### Inclusion and exclusion criteria (Aim 1)

The inclusion criterion is continuous fee-for-service Medicare enrollment for at least 12 months prior to AF diagnosis or matched index date (July 1 of inclusion year) for controls and continuous enrollment in fee-for-service (FFS) Medicare after AF diagnosis/index date for at least 12 months or until death if death occurred before 12 months of continuous enrollment.

Patients with prevalent AF will be identified as follows:ICD-9-CM code 427.31 or ICD-10-CM code I48 in 2 outpatient claims or 1 inpatient claim within 365 days, in any diagnosis position of the claim [16–18]. The index date will be the date of the first qualifying inpatient claim or second qualifying outpatient claim. Patients will be required to have 12 months of FFS claims without an AF diagnosis prior to the index AF claims based on inclusion criteria.

Exclusion criteria are:

patients with any claim for CRAO in the 12 months prior to AF diagnosis or index date for controls (July 1 of potential inclusion year).

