### Adjustment covariates

We will utilize the following pre-specified covariates for risk adjustment: age, biological sex, race/ethnicity, and cardiovascular comorbidities and medical risk factors, including the medical comorbidities included in the Charlson Comorbidity Index (except for cardiac arrhythmias, which subsumes our primary exposure of interest), and additionally including hypertension, hyperlipidemia, valvular heart disease, and smoking status, using validated ICD-9-CM and ICD-10-CM algorithms [20–23]. Carotid stenosis and Stroke/TIA are contained in the cerebrovascular disease group of the Charlson Comorbidity Index. S1 and S2 Figs show the directional acyclic graphs representing our understanding of possible confounding variables.

We will ascertain comorbidities using a twelve-month look-back period from the patient’s index date (July 1 of initial year of inclusion in cohort for controls) using established claims-based algorithms. These are outlined in Table 2, below.

**Table 2 pone.0296251.t002:** List of international classification of diseases codes used for comorbidity adjustment.

Comorbidity	ICD-9 Code	ICD-10 Code	Citation
Hypertension	401.*, 402.*, 403.*, 404.*, 405.*, 437.2*	I10.*-I13.*, I15.0, I15.2, I15.8, I15.9, I16.*, I67.4*	Birman-Deych, 2005 [21]
Hyperlipidemia†	272.x	E78.x	Oake, 2017 [22]
Tobacco Use††	305.1, 649.0x, 989.84, V15.82; CPT codes 99406, 99407, G0436, G0437, G9016, S9453, S4995, G9276, G9458, 1034 F 4004 F 4001 F	F17.x, T65.2xx, Z87.891, CPT codes 99406, 99407, G0436, G0437, G9016, S9453, S4995, G9276, G9458, 1034 F 4004 F 4001 F	Desai, 2016 [23]
Valvular Heart Disease	394.*, 395.*, 396.*, 397.*, 398.9*, V42.2*, V43.3*, 424.*	I05.*-I08.*, I09.1*, I09.81, I09.89, I09.9*, I34.*-I39.*, Z95.2*, Z95.3*, Z95.4*	Birman-Deych, 2005 [21]

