### Analytical cohort

An analytic cohort will be generated by applying the below inclusion and exclusion criteria as follows:

All patients meeting the criteria for AF in the study period and meeting other inclusion/exclusion criteria will be identified as cases, and the date of AF diagnosis will serve as case’s index date for calculation of covariates. All remaining beneficiaries will be considered potential controls; inclusion and exclusion criteria will be applied based on an index date of July 1 for each year in the study period; all beneficiaries meeting inclusion/exclusion criteria for each year will be included in the potential control pool. For all potential controls with multiple index dates/years of eligibility, the year they contribute will be selected randomly. A multivariable logistic regression analysis will be conducted using cases and potential controls to create propensity scores for AF status; the final control group will be selected using propensity score matching to the AF cases.

Survival time for patients will be defined as the number of months from the index date when criteria were met. Patients will be censored at death, at the end of fee-for-service enrollment, or at the end of data availability. When 85% of the cohort has died or been lost to follow-up, we will censor remaining patients at that point to avoid instability in estimates due to very small numbers of remaining participants.

Details of the cohort analysis will be reported using RECORD guidelines for analyses of routinely collected data, including use of a patient flow diagram [24].

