#### Regression modeling (aim 2)

a) In keeping with target trial emulation methodology as described above, the index date for patients exposed to anticoagulation will be the date of the first anticoagulant prescription drug claim occurring after the diagnosis of AF. For potential controls, only patients with no exposure to anticoagulation throughout the study period would be eligible to avoid selecting controls who start an anticoagulant during the follow-up period. For controls, inclusion and exclusion criteria will be examined for each year after AF diagnosis, and the midpoint of one random year will be selected as the index date for each control patient.b) Similar to Aim 1, patients diagnosed with CRAO precedent to or concurrent to AF diagnosis will be excluded and these patients will be examined in an exploratory analysis.c) Our primary analysis will utilize propensity score overlap weighting methodology to approximate a randomized design where baseline hazard of CRAO of patients receiving anticoagulation vs. not receiving is comparable. We will incorporate the following variables to define the propensity score: age, time since first AF claim, sex, geography, race, Medicaid dual eligibility, vascular comorbidities and non-vascular comorbidities relevant to the likelihood that a patient will be treated with anticoagulation (to include all of the comorbidity variables included for Aim 1 propensity score, as well as history of gastrointestinal bleeding or peptic ulcer disease (using validated ICD-9-CM codes 531.x (gastric ulcer), 532.x (duodenal ulcer), and 578.x (gastrointestinal hemorrhage) and their ICD-10-CM counterparts K25.x, K26.x, and K92.2) and history of intracranial hemorrhage (any of ICD-10-CM I60, I61, S06.3, S06.4, S06.5, S06.6 and their ICD-9-CM counterparts 430.x, 431.x, 432.x)) [32–35].d) Our principal effect of interest is the hazard of CRAO among patients treated with any oral anticoagulant agent compared to those not treated. Given variable patient adherence to anticoagulation, we will take advantage of the strength of Part D data (which records pharmaceutical fills rather than prescriptions) and treat anticoagulation exposure as a time-varying covariate for patients exposed to anticoagulation.e) We will perform identical sensitivity analyses as described in Aim 1.f) Table shells for the results of Aim 2 are shown in Table 8.

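### Index calendar year is in neither propensity score although the two groups get index dates by different rules, so time trends over 2000–2020 can confound both hazard ratios

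*Protocol article*

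**What the plan says.** The study covers "fee-for-service Medicare beneficiaries in the United States from 2000–2020" (Protocol article, Design and setting).

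**Index dates, Aim 1.** For AF patients, "the date of AF diagnosis will serve as" the index date (Analytical cohort). Every other beneficiary is screened at July 1 of each year. Where several years qualify, "the year they contribute will be selected randomly". Then "the final control group will be selected using propensity score matching to the AF cases". Other sections describe the control date differently. Inclusion and exclusion criteria (Aim 1) speaks of a "matched index date (July 1 of inclusion year) for controls". Adjustment covariates and Regression modeling (aim 1), item a, refer to the initial or first year in the cohort.

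**Index dates, Aim 2.** Treated patients are indexed at the first anticoagulant claim after AF diagnosis. Controls are patients never anticoagulated during the study, and "the midpoint of one random year will be selected as the index date for each control patient" (Regression modeling (aim 2), item a).

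**Score contents.** The Aim 1 list is pre-specified as "age, biological sex, race/ethnicity, and cardiovascular comorbidities and medical risk factors", spelled out as the Charlson conditions plus hypertension, hyperlipidemia, valvular disease and smoking (Adjustment covariates). Regression modeling (aim 1), item e, builds the score from that list. The outcome model in item c adjusts for age, sex, race and cardiovascular comorbidities, clustered by state. The Aim 2 score uses "age, time since first AF claim, sex, geography, race, Medicaid dual eligibility" and comorbidities (Regression modeling (aim 2), item c).

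**Coding.** The outcome code changes from ICD-9-CM to ICD-10-CM in autumn 2015, and only the ICD-9-CM code is described as validated (Outcome). Table 2 defines each comorbidity with separate ICD-9 and ICD-10 code sets.

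**The concern.** In each aim an event sets the exposed patients' index dates and a random draw sets the controls'. Nothing in those rules makes the two calendar distributions agree, and calendar year is not among the variables to be balanced. The re-estimated scores and overlap weights are meant to balance baseline covariates exactly, but that property holds only for variables in the score model.

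If CRAO is recorded more or less readily in some years, or comorbidities are captured differently under the two code systems, a difference in index years enters the comparison of AF with no AF, or of treated with untreated. It would not show in the planned output, because the shells of Tables 3 and 4 have no row for index year.

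**Working it through.** **1. Is year in any list?** Read term by term, the Aim 1 score has demographics, comorbidities and smoking. The Aim 1 outcome model has a subset of these. The Aim 2 score adds time since first AF claim, geography, dual eligibility and bleeding history. None has calendar year. Time since first AF claim measures disease duration: two patients six months after diagnosis, one in 2007 and one in 2018, have the same value.

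**2. Is year aligned in another way?** No section gives a rule for exact matching or stratification on year. The eligibility section calls the control date matched but states no matching rule, and the cohort section assigns the year at random before propensity matching.

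**3. Can the date rules produce imbalance?** The article gives no index-year distribution, so this can only be illustrated by simulation with assumed inputs.
- *Aim 1.* Assumptions: 45% enrolled at the start of 2000, the rest entering evenly; mean stay 9 years; constant AF hazard of 0.03 per year after the first year. Mean index year was nearly equal (standardized difference 0.004), yet 20% of AF patients and 25% of controls were indexed in 2015 or later.
- *Aim 2.* Assumptions: AF diagnoses spread evenly from 2000 or 2006 to 2020; mean follow-up 6 years; treatment starting on average 0.4 years after diagnosis; share treated flat at 55%, or rising from 50% to 60% or from 40% to 70%. Standardized differences in index year ran from −0.02 to −0.42 (controls later), before any adjustment for time since first AF claim. The widest split after the code change was 31% of treated v 45% of controls.

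**4. What would an imbalance do?** The plan has no figure for this. Let pE and pC be the late-era shares of exposed and controls, and r the late-to-early ratio of the recorded CRAO rate. With a true hazard ratio of 1, the observed ratio is about

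B = [1 + pE(r − 1)] / [1 + pC(r − 1)].

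For 60% v 40% and r = 1.5: (1 + 0.30)/(1 + 0.20) = 1.083.

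| pE v pC (assumed) | r = 0.5 | r = 1 | r = 1.5 | r = 2 |
|---|---|---|---|---|
| 20% v 25% | 1.029 | 1.000 | 0.978 | 0.960 |
| 31% v 45% | 1.090 | 1.000 | 0.943 | 0.903 |
| 55% v 45% | 0.935 | 1.000 | 1.041 | 1.069 |
| 60% v 40% | 0.875 | 1.000 | 1.083 | 1.143 |

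The term vanishes when r = 1 or when pE = pC. Balancing on index year brings about the second condition. The formula places all follow-up in the index era. Patients indexed before the code change can be followed past it, so index-year shares only approximate person-time by era.

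**5. Scale against sampling error.** The sample size section gives 285,000 per group and rates of 22 and 11 per 100,000 per year. With an assumed 4 years of follow-up, events are 285,000 × 4 × 0.00022 = 250.8 and 285,000 × 4 × 0.00011 = 125.4. The standard error of the log hazard ratio is √(1/250.8 + 1/125.4) = 0.109. The 1.083 case is then ln(1.083)/0.109 = 0.73 standard errors. The 0.978 case is 0.21 standard errors in the other direction.

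**The case against.** The strongest reply is that omitting year is not itself bias. Confounding needs both an index-year imbalance and a time trend in recorded CRAO or in comorbidity capture, and the article shows neither. That stands, and it limits the claim to what can happen.

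Three stronger readings are tempting, and the documents do not support them.
- *Era differences do confound both aims, with a known direction.* The late-era shares and the rate ratio have no source in the article. The Aim 1 simulation put controls later after 2015, and most Aim 2 runs also put controls later, but with other assumed shares the sign reverses.
- *The bias reaches about one standard error.* This needs 60% v 40%, r = 1.5 and about 600,000 AF patients at once: 528 and 264 events over 4 years, standard error 0.075, ln(1.083)/0.075 = 1.06. The 600,000 is not in the article, which gives 285,000 for power and 818,940 from a query.
- *Changing anticoagulant uptake passes directly into the hazard ratio.* In Aim 2 uptake is the exposure, and a change in it confounds only if CRAO risk or recording also changes over time. In Aim 1 anticoagulation follows AF and is not a baseline confounder of it. Table 1 lists drugs without dating their use.

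Some safeguards help in part. Time since first AF claim may absorb some of the lag between the Aim 2 date rules. The stroke and urinary tract infection control outcomes could flag an era effect if their coding shares the trend in CRAO, but they would not remove it. The confounding diagrams (S1 and S2 Figs) are not shown, but the text itself fixes the score variables, so this is not a detail left to a fuller plan.

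**Conclusion.** The point holds as a possible and easily avoided source of confounding. Index year is absent from both enumerated scores and from the Aim 1 outcome model, index dates follow different rules by group, and nothing else aligns year across a period with a documented change of code system. Overlap weighting as planned does not guarantee balance on year.

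The size and sign of any bias cannot be derived from the article. Under the moderate assumed inputs in the table it runs from a few percent to somewhat over 10% of the hazard ratio, either way, and it is nil if the year distributions agree or there is no trend. Only the code change is documented as a possible cause of a trend. Aim 2 also needs Part D data, so its calendar span may be shorter than 2000–2020; the article does not say.

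**What to change.** 1. Add index calendar year, as a categorical variable, to the Aim 1 matching score (or match exactly on year), to the re-estimated Aim 1 score and to the Aim 2 score.
2. Add index year to the shells of Tables 3 and 4 and report its standardized difference.
3. Settle the control index year in Aim 1. The eligibility section implies a matched date, the cohort section a random eligible year, and the covariate and regression sections the initial or first year. If the last means the earliest eligible year, control dates can only be the same as or earlier than under the random draw. If it means the single year contributed, the text should say so.

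Index year is known for every patient, so no new data are needed. The possible cost is some loss of precision in Aim 2 if year predicts treatment strongly and CRAO weakly. That loss cannot be computed from the article and is likely to be small.

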### Statistical analysis plan

#### Re-estimation of propensity scores and overlap weighting

To adjust for the observed confounding and focus on the patient population in clinical equipoise, we will first re-estimate the propensity scores in the matched sample and then apply propensity score overlap weighting [25–27] to ensure exact balance of baseline covariates between patients with and without AF.

#### Descriptive analysis

Using the weighted analytic cohort, we will calculate means with standard deviations and medians with interquartile ranges to summarize the distribution of continuous, normally distributed variables, and medians with interquartile ranges to summarize the distribution of continuous, not normally distributed variables. We will summarize categorical data using counts with percentages. Data will be stratified by presence of atrial fibrillation and include key demographic and clinical factors. For Aim 2, we will additionally summarize anticoagulant usage patterns among patients with atrial fibrillation, including class of agent utilized (DOAC vs. warfarin), number of monthly fills per calendar year, and duration of exposure in months. Table shells are provided in Tables 3–5.

**Table 3 pone.0296251.t003:** Characteristics of the overlap-weighted primary analysis cohort defined at first date of meeting study eligibility.

Characteristic	Total Sample (N = xxxx)	Patients with AF (n = xxxx)	Patients without AF (n = xxxx)	Standardized Difference
Age, mean (SD)				
Women, n (%)				
Race/ethnicity, n(%)				
Asian/Pacific Islander				
Black, non-Hispanic				
Hispanic				
White, non-Hispanic				
Comorbidities (n, %)				
Cerebrovascular Disease				
Chronic Kidney Disease				
Congestive Heart Failure				
Coronary Artery Disease				
Diabetes Mellitus				
Hyperlipidemia				
Hypertension				
Peripheral Vascular Disease				
Smoking				

**Table 4 pone.0296251.t004:** Characteristics of the secondary analysis (Part-D enrolled) cohort defined at first date of meeting study eligibility.

Characteristic	Total Sample (N = xxxx)	Patients with at least one fill for anticoagulant (n = xxxx)	Patients without any anticoagulant use (n = xxxx)	Standardized Difference
Age, mean (SD)				
Women, n (%)				
Race/ethnicity, n(%)				
Asian/Pacific Islander				
Black, non-Hispanic				
Hispanic				
White, non-Hispanic				
Comorbidities (n, %)				
Cerebrovascular Disease				
Chronic Kidney Disease				
Congestive Heart Failure				
Coronary Artery Disease				
Diabetes Mellitus				
Hyperlipidemia				
Hypertension				
Peripheral Vascular Disease				
Smoking				
Antiplatelet agent use				
Oral anticoagulant use				
Lipid-lowering agent				
Oral hypoglycemic agent				
Oral antihypertensive agent				

**Table 5 pone.0296251.t005:** Anticoagulation usage patterns among patients with atrial fibrillation with at least one Part D fill for an anticoagulant medication.

Characteristic	Total Sample (N = xxxx)
Number of monthly fills per calendar year (mean, SD)	
Class of Anticoagulant Agent	
DOAC	
Warfarin	
Specific Anticoagulant Drug Used	
Apixaban	
Dabigatran	
Edoxaban	
Rivaroxaban	
Warfarin	
Duration of Anticoagulant Exposure (months, mean, SD)	
Concurrent use of antiplatelet agent (count, %)	

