#### Regression modeling (aim 1)

a) The study index date will be the date of the first AF claim in the study and July 1 in the first year of inclusion in the analytic cohort for controls for the purposes of our survival analysis.b) We will describe cumulative incidence of CRAO over time with the overlap-weighted cumulative incidence function and presented graphically for patients with and without atrial fibrillation. Next, a weighted, unadjusted cause-specific hazard model will be fit with AF as the univariable predictor and CRAO as the event of interest, with patients censored at death, at end of data availability, or at end of fee-for-service Medicare enrollment.c) Then, a weighted cause-specific hazard model, clustered by state, and adjusting for age, sex, race, cardiovascular comorbidities will be fitted. Directly adjusted cumulative incidence curves for AF and control patients will be created with adjustment for all model covariates [28].d) We will test the proportional hazards assumption for all models.e) Our primary analytical model will be an overlap-weighted model with propensity scores derived from the adjustment covariates previously described as predictors for the presence of atrial fibrillation. We will report our results with sequential adjustment to produce the fully-adjusted, weighted model. We employ this sequential adjustment strategy to provide insight as to sources of measured confounding.f) We will evaluate **positive control endpoints**. Our positive control endpoints will be any ischemic stroke (defined by ICD-9-CM 434.0, 434.00, 434.10, 434.11, 434.9, 434.90, 434.91, 436/ ICD-10-CM I66.09, I66.19, I66.29, I66.9, I63.40, I63.50, I67.89 in the primary diagnosis position in a hospitalization or ED visit) [29]. We will utilize the same modeling strategy as used for the primary outcome.g) We will evaluate **negative control (falsification) endpoints**. Our negative control endpoint will be hospitalized/ED urinary tract infection (including renal abscess and pyelonephritis) (ICD-9-CM 590.1, 590.11 590.2, 590.8 or 599.0/ ICD-10-CM N15.1, N39.0, N10). We will utilize the same modeling strategy as used for the primary outcome [30].h) We will perform several sensitivity analyses for outcome ascertainment.

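### Tables 3 and 4 report coronary artery disease, but the adjustment list covers coronary disease only through myocardial infarction codes

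*Protocol article*

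**What the plan says.** Under Adjustment covariates, the pre-specified set is age, sex, race/ethnicity and the Charlson comorbidities, "additionally including hypertension, hyperlipidemia, valvular heart disease, and smoking status". Table 2 in that section is captioned "List of international classification of diseases codes used for comorbidity adjustment". Its myocardial infarction row uses ICD-9 410 and 412 and ICD-10 I21, I22 and I25.2. No row covers angina or chronic coronary disease without infarction.

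Under Descriptive analysis, the plan states "Data will be stratified by presence of atrial fibrillation and include key demographic and clinical factors". The shells that follow (Table 3 for the overlap-weighted Aim 1 cohort, Table 4 for the Part D cohort) contain a "Coronary Artery Disease" row and no myocardial infarction row.

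The Aim 1 primary model uses "propensity scores derived from the adjustment covariates previously described as predictors for the presence of atrial fibrillation". The purpose given for re-estimating the scores and applying overlap weights is to "ensure exact balance of baseline covariates between patients with and without AF". The Aim 2 score takes over all the Aim 1 comorbidity variables and adds others, none of them coronary.

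**The concern.** Myocardial infarction is a subset of coronary artery disease, not another name for it. A patient with coronary disease and no infarction code in the twelve-month look-back enters the score only as someone without infarction; nothing in the score marks the coronary disease.

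This matters for two reasons. First, Aim 1 asks whether AF is a risk factor independent of other vascular risk factors, and the Introduction criticises an earlier cohort study for not adjusting for them. A vascular condition that is more common with AF and raises CRAO risk would, if left out, push the AF hazard ratio upward. Second, Table 3 is the weighted table with a standardized-difference column. A wider coronary row could show an imbalance in the very table meant to demonstrate balance.

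**Working it through.** The plan gives no figure on this point, so there is none to reproduce. The check has three parts.

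**1. Reported rows against adjusted rows**

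| Row in Tables 3 and 4 | Entry in Table 2 | Same condition? |
|---|---|---|
| Chronic kidney disease | Renal disease | Essentially |
| Diabetes mellitus | Two diabetes rows | Yes, combined |
| Smoking | Tobacco use | Essentially |
| Coronary artery disease | Myocardial infarction only | No, a subset |

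The text says that carotid stenosis and stroke/TIA fall within the cerebrovascular group. It gives no such mapping for coronary disease.

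**2. What overlap weights balance**

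With AF indicator Z, fitted logistic score e and covariate x in the model, the likelihood equations give Σ(Z − e)x = 0. This rearranges to ΣZ(1 − e)x = Σ(1 − Z)e·x. The overlap weights are 1 − e for AF and e for controls, so the weighted means are equal for every term in the model, and for no other term by construction.

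A simulation of 400,000 people illustrates this. All inputs are assumed: coronary disease in 30–40%, infarction in 25–30% of those, a coronary–AF odds ratio of 1.5–2.0, and one further covariate. The score holds infarction but not coronary disease.

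| Prevalence; odds ratio | Infarction std. diff. | Coronary disease, AF vs control (weighted) | Coronary disease std. diff. |
|---|---|---|---|
| 30%; 1.5 | 0.000 | 0.365 vs 0.294 | 0.15 |
| 30%; 2.0 | 0.000 | 0.397 vs 0.274 | 0.26 |
| 40%; 2.0 | 0.000 | 0.501 vs 0.370 | 0.27 |

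With coronary disease added to the score, both standardized differences are 0.000 in all three settings.

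**3. Possible size of bias**

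For a rare outcome and a binary omitted factor with rate ratio r, the bias factor is (1 + p1(r − 1)) / (1 + p0(r − 1)), where p1 and p0 are the weighted prevalences in AF and control patients.

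Assume coronary disease without infarction at p1 = 0.40, p0 = 0.25 to 0.30 and r = 1.3 to 1.5:
- p0 = 0.30, r = 1.3: 1.12 / 1.09 = 1.028
- p0 = 0.25, r = 1.5: 1.20 / 1.125 = 1.067

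With the simulated prevalences and r = 1.5 to 2.0, the factor runs from 1.031 to 1.097.

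Against the planning hazard ratio of 2, factors of 1.028 and 1.067 would give 2 × 1.028 = 2.06 and 2 × 1.067 = 2.13.

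The simulation has only one other covariate. The real score also holds heart failure, peripheral vascular disease, diabetes and more, so the true residual gap may well be smaller.

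**The case against.** **The row may simply be the infarction variable.** The shells rename other Table 2 entries, and no infarction row appears in Tables 3 or 4. If so, the row is in the score and is balanced, and the fault is the label. This reading cannot be excluded. It does not dispose of the point, because coronary disease without infarction is outside the printed score either way.

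**A reported factor need not be an adjusted one.** Table 4 also lists antiplatelet, lipid-lowering, hypoglycemic and antihypertensive drugs, which the Aim 2 score does not name. This is fair as a general rule. The coronary row differs in that Table 2 adjusts for part of the same condition.

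**A reader might infer that the exact-balance statement is false.** The documents do not support that. Read with the Aim 1 model description, it covers the modelled covariates, for which it is correct. It also concerns AF against no AF only, so it does not extend to Table 4, which compares anticoagulant groups and is not titled as weighted.

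**The plan has checks.** The standardized differences would expose an imbalance in the row, the control endpoints probe residual confounding, and the Limitations section acknowledges that it may remain. These help to detect or interpret a problem; they do not remove it.

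**Some material is not visible.** The causal diagrams (S1 and S2 Figs) are not shown. However, the mismatch lies between two items that the article prints in full.

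**Conclusion.** The mismatch stands as a minor point. The reported coronary factor is undefined, and the adjustment list reaches coronary disease only through infarction. If the row is wider than infarction, its balance in Table 3 is not guaranteed, and residual confounding of the AF hazard ratio is possible. The Aim 2 score carries the same omission.

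The range of 1.03 to 1.07 rests wholly on assumed prevalences and rate ratios; the documents supply none of them. It is small beside the planning hazard ratio of 2.

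A reader might go further and conclude that the AF effect will not be independent of coronary disease, or that the row will certainly be unbalanced. Neither follows. Infarction, heart failure, peripheral and cerebrovascular disease, hypertension, hyperlipidemia, diabetes, renal disease and tobacco use are all in the adjustment list and capture part of coronary disease. The Aim 1 outcome model, described only as "adjusting for age, sex, race, cardiovascular comorbidities will be fitted", does not itemise its comorbidities and so does not settle the matter either way.

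**What to change.** Add a coronary artery disease row with ICD-9 and ICD-10 codes to Table 2. Enter it in the Aim 1 and Aim 2 propensity scores and in the adjusted hazard models, so that the factor reported in Tables 3 and 4 is the one adjusted for. If only infarction is intended, relabel the row as myocardial infarction in both shells; that corrects the reporting but leaves coronary disease without infarction unadjusted.

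The cost is one more claims-based covariate over the same look-back, or a changed label. No new data are needed, and the stated timeline places the primary analyses after publication of the protocol.
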